**Figure 1 F1:**
[figure not shown]
The flow chart.

### Ethics

The trial will be conducted in accordance with the principles of the Declaration of Helsinki and has been approved by the review boards and ethics committees of the 12 centers (Ethics approval numbers: 2013EC061-01; 2013AH-015; B2013-00084-01; HBZY2013-C025-01; HN-LL-KY-2013-004-01; 2013EC002; 2013020-KY; 2013EC061-01 (20130515); 20130419; 20130620; 2013001; ZSLL-KY-2013-001) (Additional file 1).

### Participants

In total, 360 participants will be recruited in this trial.

#### Inclusion criteria

Participants conforming to all the following conditions will be included: i) cycle irregularity (period occurring 7 days earlier or later) in the past 12 months (early MT) and the last menstruation being at least 2 months previously, but no longer than 11 months previously in the past 12 months (late MT); ii) MT symptoms such as hot flashes, sweating, sleep disturbance, migraine, anxiety, vaginal dryness, and sexual problems; iii) aged 40 to 55 years old; iv) negative pregnancy test; and v) participation is voluntarily and the informed consent signed.

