## Background

The menopausal transition (MT) period refers to the time from the commencement of variations in menstrual cycle length and a monotropic rise in follicle-stimulating hormone to the final menstrual period. It is further divided into two phases: the ‘early MT’ in which cycle lengths vary by more than 7 days from the typical length for the individual woman and the ‘late MT’ , characterized by at least two skipped cycles and at least one period of amenorrhea exceeding 60 days [1-4]. Different symptoms appear during different phases of the MT period. Hot flashes are the most frequent symptom and the prevalence of flashes can be as high as 79% at the completion of menopause [5,6]. Other symptoms include night sweats, sleep disturbances, vaginal dryness, urinary incontinence, weight gain, fatigue, irritability, and anxiety. Studies find that most women experience at least one or more of these symptoms as they transit through the postmenopausal stage of life [7].

Hormone therapy (HT) is the recommended drug for women with symptoms related to postmenopause [8]. Because of its long-term risks, HT is no longer prescribed as preventive therapy, but rather for managing menopausal symptoms [9]. Treatment of the perimenopausal woman represents a greater challenge than the menopausal woman because of unpredictable and unstable ovarian function [10]. A study of women’s decision making during the MT has shown that participants believe that menopausal symptoms are best managed with a natural product rather than HT [11].

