## Methods/design

This will be a prospective RCT conducted over 2 years (from June 2013–May 2015) and at 12 hospitals in China (Guang’anmen Hospital; The First Hospital Affiliated to Anhui University of Chinese Medicine; Guangdong Provincial Hospital of Traditional Chinese Medicine (TCM); Hubei Province Hospital of TCM; The First Hospital of Hunan University of Chinese Medicine; Hengyang Hospital of Hunan University of Chinese Medicine; Affiliated Hospital of Shandong University of TCM; Integrated TCM and Western Medicine of Shanxi University of TCM; Shanxi Province Hospital of TCM; Yueyang Hospital of Shanghai University of TCM; TCM Hospital of Yantai; and 3rd Hospital of Zhejiang Chinese Medical University).Participants experiencing MT will be recruited from the 12 centers by use of advertisements in newspapers, television, websites, and posters. Participants will be sent to a gynecologist who will make the diagnosis. A 1-week baseline assessment will include MRS, Menopause-Specific Quality of Life Questionnaire score (MENQOL), average 24-h hot flash score, and hormone levels (FSH, LH, FSH/LH, and E2, examined at days 2 to 4 of the menstrual period or any day for participants in menopause). Eligible participants will be randomized after their informed consents are obtained. Central randomization will be performed by the Clinical Evaluation Center of the China Academy of Chinese Medical Sciences in Beijing. Stratified block randomization will be made according to the hospital and a block size of six will be used. A random number will be immediately received by the acupuncturist by phone or online after the informed consent is signed. All of the participants, statisticians, outcome assessors, and the gynecologists are blinded to the allocation, except for the acupuncturists. The flowchart of the trial is presented in Figure 1.

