5. Analysis of primary outcome: the primary outcome is the change in MRS compared with baseline at the 8th week (the primary time frame) and at the 4th, 20th, and 32nd week (the secondary time frame). Analysis of covariance (for normal distributed data) or nonparametric tests (for abnormal distributed data) will be used to investigate whether EA is more effective than sham EA. To detect the center effect, a covariance model will be used. Further analysis will be done if there is a center effect.

6. Analysis of secondary outcomes: for each group, the mean 24-h hot flash score, MENQOL, and hormones will be compared with their baseline. A *t*-test or nonparametric test will be used for comparison between groups.

7. Subgroup analysis: subgroup analyses will be conducted according to the stage of MT (early stage and late stage) to observe EA’s influence on MRS and MENQOL at the 4th, 8th, 20th, and 32nd week for participants. Analysis of covariance or nonparametric tests will be used.

8. Analysis of blinding: the number and percentage of subjects choosing true EA in the two selected centers will be established. A χ^2^ test or nonparametric test will be used for comparison among groups.

9. Analysis of safety: according to adverse events listed in the case report form, an analysis will be done using the χ^2^ test or the Fisher exact test.

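### Inclusion criterion i joins the early-MT and late-MT definitions with *and*, so read literally it admits only late-MT women and contradicts the planned early/late subgroup analysis

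*Protocol article*

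**What the plan says.** The inclusion list opens with a rule that applies to every item: "Participants conforming to all the following conditions will be included". Its first item has two limbs, each with its own stage label. The first is "cycle irregularity (period occurring 7 days earlier or later) in the past 12 months (early MT"). The second follows at once: "and the last menstruation being at least 2 months previously, but no longer than 11 months previously in the past 12 months (late MT"). The join between the two reads "in the past 12 months (early MT) and the last menstruation being at least 2 months previously".

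The Background says of the transition: "It is further divided into two phases". Early MT is the phase "in which cycle lengths vary by more than 7 days from the typical length for the individual woman". Late MT is marked by two or more missed cycles together with an episode of amenorrhea longer than 60 days.

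Item 7 of the statistical analysis states that "subgroup analyses will be conducted according to the stage of MT (early stage and late stage"), for MRS and MENQOL at weeks 4, 8, 20 and 32.

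Baseline hormones are "examined at days 2 to 4 of the menstrual period or any day for participants in menopause". The Outcome section uses a similar clause for week 8.

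**The concern.** Two definitions that the Background gives as alternatives are both required of the same woman. Someone with irregular cycles who menstruated last month is in early MT by the Background, yet she fails the second limb and so fails the criterion. Applied as written, the rule gives a late-MT trial, while the objectives, the Discussion and the subgroup plan describe a trial across MT.

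Three things would then be affected: who is studied, whether the stage subgroups exist, and whether the result can be stated for MT in general. An analysis plan cannot repair this later, because it cannot supply early-MT women whom the eligibility rule turned away.

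**Working it through.** No stated figure needs reproducing, because the point does not depend on sample size, power or alpha. The check is a truth table of criterion i, followed by a comparison with the other sections.

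**Inputs.** A = irregular cycles in the past 12 months (labelled early MT). B = last menstruation 2 to 11 months ago (labelled late MT). Both come from the Inclusion criteria.

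| A | B | A *and* B (as written) | A *or* B |
|---|---|---|---|
| no | no | not eligible | not eligible |
| yes | no | not eligible | eligible |
| no | yes | not eligible | eligible |
| yes | yes | eligible | eligible |

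**Step 1.** As written, the only eligible row has B true. The row that describes early MT alone (A yes, B no) is excluded.

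**Step 2.** The two limbs overlap. Take 2 months as about 60 days. A woman who has gone that long without a period is more than 7 days late if her usual cycle is shorter than 60 − 7 = 53 days. So, on that assumption, B nearly always brings A with it. The literal criterion then reduces to the late limb. Under *or*, most late-MT women would meet both limbs, so the labels alone do not assign a stage.

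**Step 3.** Set this against item 7: 2 stages × 2 outcomes × 4 visits = 16 stage-specific comparisons. With everyone meeting B, the early stratum has 0 of 360 women and its 2 × 4 = 8 comparisons have no data. The other 8 are made in the whole trial population, so they are not subgroup analyses.

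**Step 4.** Look for a repair elsewhere. Exclusion i, on regular cycles in the 3 months before enrollment, does not say that either limb is enough, and under the literal reading it would have little left to exclude. Two other places sit better with menstruating participants: baseline hormone sampling early in a period, and the provision for women who are bleeding or decline needling during a period. They point to *or* but do not state it.

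**Step 5.** Compare the two definitions of late MT. The Background asks for at least one long amenorrhea and does not require it to be current. Criterion i uses the present interval since the last period. A woman who had such an episode with two or more missed cycles, and who has since resumed bleeding, is late MT by the Background but does not meet the limb labelled late MT.

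**The case against.** The strongest reply is that this is a slip of wording. Each limb carries its own label, so *and* can be read as listing the two kinds of women admitted. The subgroup plan presupposes both stages, a gynecologist makes the diagnosis, and staff from all 12 centers are trained beforehand. The article also condenses a fuller protocol that is not shown. Most of this stands: *or* was almost certainly meant. It does not remove the contradiction, because the article states the eligibility rule in operative form and no section corrects it.

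A reader might infer more than the documents support:

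- **That early-MT women were turned away, or that centers differed in how they read the rule.** Nothing shows how any center applied it. Trial status reports 80 women recruited but not the wording they were screened under.
- **That the treatment comparison is biased.** Eligibility is settled before randomization, and randomization is stratified by hospital, so the comparison within each hospital stays valid on either reading.
- **That late-MT women have no valid hormone-sampling day, so that their data depend on bleeding after randomization.** This takes *in menopause* strictly. With time since last period capped at 11 months and all participants meant to be in the transition, the strict sense would cover nobody at baseline. The reading that gives the clause a use is women who are not bleeding. The term is loose and worth clarifying, but the selection argument does not follow.

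**Conclusion.** The criterion is wrong as written. Under its literal reading the early stratum is 0 of 360 and 8 of 16 stage-specific comparisons are void. Those figures are conditional on centers following the text, which the documents neither show nor rule out. The contradiction between the Inclusion criteria, the Background and item 7 needs no such assumption.

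The consequence is confined to the population studied, the stage subgroup analysis and generalisation to MT as a whole. The randomized comparison and the required sample size are unaffected.

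**What to change.** Reconcile the Inclusion criteria, the Background and item 7:

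1. State in criterion i whether meeting either limb is enough.
2. Give one baseline rule for staging a woman as early or late that agrees with the Background definition. It must cover women who meet both limbs and women who have resumed bleeding after a long amenorrhea. Simply splitting at 2 months since the last period would not do, because it would stage the second group differently from the Background.
3. Record stage at baseline, and apply the rule to women already enrolled (80 at the time of the article).
4. As a minor point, say whether *in menopause* in the hormone-sampling clauses covers late-MT women who are not bleeding.

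The cost is a short amendment, a note to 12 centers and a check of the records of the 80 women. It is cheapest now, with 360 − 80 = 280 still to recruit by the article's count. Stage can be recovered later if last-period and cycle histories were recorded. Any woman wrongly screened out cannot be.

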#### Exclusion criteria

Participants with the following conditions will be excluded: i) regular cycles during the past 3 months before enrollment; ii) use of estrogen, serotonin-reuptake inhibitors, soybean isoflavone, progestin, vitamin E, or black sesame in the past 4 weeks; iii) presence of ovarian cyst, uterine myoma (diameter ≥4 cm), or after hysterectomy/ovariectomy; iv) participants with a radiochemotherapy history or undergoing radiochemotherapy; v) cryptogenic vaginal bleeding; vi) coagulation disorder or use of anticoagulants like warfarin and heparin sodium; vii) existing skin diseases like eczema or psoriasis; viii) severe hepatic/renal insufficiency; ix) insufficiently controlled hypertension, diabetes, or thyroid diseases; x) existing diabetic neuropathy, malignant tumor, and psychiatric disorders; xi) desire to become pregnant or pregnant or breast-feeding; xii) regular use of sedatives or anxiolytics; xiii) smoking or heavy alcohol intake; xiv) mandatory indication for HT (e.g., postsurgical menopause or active osteoporosis); and xv) presence of a cardiac pacemaker or artificial joint.

### Interventions

The regimen will be based on a Chinese literature review from the previous 10 years, our phase I trial and specialist’s consensus. Acupuncturists with over 2 years working experience and academic credentials above an undergraduate degree in each hospital will be trained with the protocol before the start of the trial. One session will be given every other day, three sessions per week (24 sessions in all), and each session will last for 30 minutes. A reserved time is made for treatment to prevent participants from communicating with each other.

### Electroacupuncture group

Acupoints RN4, EX-CA1, ST25, and SP6 on double sides are used. Stick adhesive pads (Figure 2) are placed at all points. For ST25, EX-CA1, and RN4, the needle will be inserted (75 mm) vertically through the pads and quickly through the skin, and then slowly and vertically penetrate through the layer of fatty tissue, up into the muscles of the abdominal wall (until the moment of resistance is sensed on the tip of the needle and the participant feels a sting). For RN4, the needle will be manipulated slightly with an even lifting, thrusting, and twisting method, repeated three times. The needle will be inserted (40 mm) vertically at SP6 to a depth of 1 *cun*. The needle will be manipulated slightly with an even lifting, thrusting, and twisting method repeated three times to reach de-qi. The electric stimulator will be put on the EX-CA1 and ST25 points with a dilatational wave, 10/50 Hz, 0.1 to 1.0 mA. The current intensity will be increased until the abdomen shivers. The needles are left for 30 minutes and the same manipulation methods for RN4 and SP6 will be given every 10 minutes (three times in all) (Figure 3).

**Figure 2 F2:**
[figure not shown]
**Adhesive pad.** The adhesive pad used in the trial. The bottom face is adhesive and sticks to the skin.

**Figure 3 F3:**
[figure not shown]
Some points used in the trial.

### Sham-electroacupuncture group

Non-points proximate to RN4 (P1), EX-CA1 (P2), ST25 (P3), and SP6 (P4) on double sides will be used. P1 and P3 are at the sites 1 *cun* (outward in horizontal direction) proximate to RN4 and ST25, respectively. P2 is 2 *cun* (outward in horizontal direction) proximate to EX-CA1. P4 is at the middle site of the spleen meridian and the kidney meridian (backward in the horizontal direction proximate to SP6). Adhesive pads will be applied to all points. Blunt needles will be inserted but not to pierce the skin.

The needle will be manipulated slightly with an even lifting, thrusting, and twisting method repeated three times for each point. The sham electric stimulator will be put on P2 and P3 with the same parameters as the EA group, but without current intensity. The needles will be left for 30 minutes and the same manipulation methods for all points will be given every 10 minutes. Every point will be checked after treatment to make sure there is no needle hole in the skin.

For participants undergoing bleeding, treatment will be provided. However, for individual participants who do not want needling during their periods, the treatment and outcome assessment will be postponed.

Other MT-relevant treatments will not be allowed throughout the trial. For any use of other treatments, information should be recorded on the case report form in detail. The proportion of participants using other MT-relevant treatment will be compared between groups.

### Outcome

The primary outcome is the change in the MRS compared with baseline at the 8th week (the primary time frame) and at the 4th, 20th, and 32nd week (the secondary time frame). The secondary outcomes include changes in the average 24-h hot flash score [22] (1-week sum score divided by 7, evaluated at the 4th, 8th, 20th, and 32nd week), MENQOL (at the 4th, 8th, 20th, and 32nd week), and FSH, LH, FSH/LH, and E2 (examined at days 2 to 4 of the menstrual period or for participants in menopause, at the end of the 8th week) compared with baseline.

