## Discussion

In such a large scale RCT, we want to observe EA’s influence on symptoms and quality of life for MT patients. In this trial, not only hot flashes, but also MRS, MENQOL score, and hormone levels will be evaluated. With specific inclusion criteria, only women experiencing MT are included. For the placebo control, we use non-points and a tailor-made sham needle. This needle is different from the retractable needle usually used for sham acupuncture [24,25]. The needle in this trial is more simply constructed and more acceptable to Chinese people. The patent application for the needle is in process. With the use of adhesive pads and a sham electric stimulator, the appearance of the needles and the electric stimulator look exactly alike in the two groups, thus allowing better blinding of the participants. Participants will be treated alone in a treatment room at one time to avoid any communication between them. Though there is no completely inert placebo acupuncture and blinding is difficult in acupuncture trials, the placebo effect of EA can still be partially excluded in this study.

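### The hormone sampling rule covers menstruating women and women in menopause, but assigns enrolled late-transition women with 2 to 11 months of amenorrhoea to neither category

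*Protocol article*

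**What the plan says.** The protocol article states the timing of hormone samples twice.

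- **Baseline (Methods/design):** samples are "examined at days 2 to 4 of the menstrual period or any day for participants in menopause", as part of a baseline assessment lasting one week.
- **Week 8 (Outcome):** samples are "examined at days 2 to 4 of the menstrual period or for participants in menopause, at the end of the 8th week". The any-day allowance is not repeated.

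Three other places say who is in the trial.

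- **Inclusion criteria**, for the late stage: "the last menstruation being at least 2 months previously, but no longer than 11 months previously in the past 12 months (late MT").
- **Background**, defining the late stage: "characterized by at least two skipped cycles and at least one period of amenorrhea exceeding 60 days". It also places the end of the transition at the final menstrual period.
- **Discussion:** "With specific inclusion criteria, only women experiencing MT are included".

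Under Sample size and statistical analysis, item 6 compares hormones with baseline within each group, and between groups by a t-test or nonparametric test. Item 7 plans early-stage and late-stage subgroups for MRS and MENQOL, not for hormones.

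**The concern.** One of the two sampling categories describes women whom the trial does not set out to enrol, while a stage that it does enrol is named in neither. A woman who has not bled for several months generally cannot give a day 2 to 4 sample within a one-week baseline, and may not be able to at week 8. Staff at 12 hospitals would then either leave her unsampled or decide locally that the menopause category applies to her.

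What is at stake is the interpretation of FSH, LH, FSH/LH and E2, which the article lists within its second objective. Samples fixed to the early cycle and samples taken on any day are different measurements. If a woman moves from one type to the other between visits, her change score combines change over time with change in cycle timing. The planned between-group test takes no account of sampling type or transition stage.

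**Working it through.** The article gives no figure to reproduce here. The check is a comparison of sections, plus simple date arithmetic.

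**Step 1: baseline.** The Inclusion criteria cap time since the last period at 11 months and label women between 2 and 11 months as late transition. The Discussion says that only women in transition are included. On the trial's own labels, no enrolled woman is in the menopause category at entry. Late-stage women who do not bleed during the baseline week are not in the day 2 to 4 category either, so the rule places them nowhere.

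**Step 2: week 8.** Eight weeks is 56 days, and 56 / 30.4375 = 1.84 months. A woman who stays amenorrhoeic moves from 2 to 11 months at entry to:

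- shortest: 2 + 1.84 = 3.84 months
- longest: 11 + 1.84 = 12.84 months

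The article does not state how long amenorrhoea must last to count as menopause. Assume 12 months, which fits the 11-month entry limit. To reach it by week 8 a woman needs more than 12 − 1.84 = 10.16 months at entry. If entry durations among women who stay amenorrhoeic are uniform over the 9-month range (also an assumption), the share who reach it is (11 − 10.16) / 9 = 0.84 / 9 = 0.093, or about 9%. The other 91% or so are in neither category at week 8.

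Sensitivity to the threshold: if menopause began as soon as the 11-month entry limit was passed, the entry duration needed would be 11 − 1.84 = 9.16 months. The share would be 1.84 / 9 = 0.204, about 20%, leaving about 80% in neither category. Durations concentrated near 2 months would lower the share reaching menopause; durations concentrated near 11 months would raise it.

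**Step 3: how many women.** The late-stage share of the 360 participants is not given. Each 10 percentage points is 0.10 × 360 = 36 women. A purely illustrative share of 30% to 50% would be 108 to 180 women, less those who happen to bleed in the sampling window.

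**Step 4: consequence under each reading.**

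| Reading of the menopause category | Late-stage woman, no bleeding | Late-stage woman whose periods return by week 8 |
|---|---|---|
| Literal | No valid baseline sample; usually none at week 8 | Week-8 sample on days 2 to 4, with no valid baseline |
| Loose (not currently menstruating) | Untimed sample at both visits | Untimed at baseline, days 2 to 4 at week 8 |

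The loose reading removes most of the gap but leaves a mixture of sampling types that the item 6 test ignores. Randomisation is stratified by hospital, not by stage, so stage is balanced between groups only on average.

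**The case against.** The strongest reply is that the authors meant menopause loosely, as not currently menstruating. In a trial restricted to the transition, the category has a clear use only on that reading, and the two timing rules then fit together: days 2 to 4 for women with periods, any day at baseline and the end of week 8 for the rest. Moreover, if the transition ends at the final menstrual period, an amenorrhoeic woman whose last bleed was her final one has already left it. This reading is plausible. It is not written, however, and it sits badly with eligibility criteria that call the same women late transition.

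A second reply also stands in part: visit windows and fallback rules are details that an article may leave to the full protocol. Their absence is not counted here. The point is that the category as stated does not match the enrolled population.

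A reader might infer more than the documents support:

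- **That the menopause category is always empty.** It is empty at entry on the trial's labels, but a minority could enter it by week 8.
- **That every participant is affected**, because the two parts of the first inclusion criterion are joined by a conjunction. The planned early and late subgroups show that this is not the intended meaning.
- **That the hormone results will be biased between groups**, because electroacupuncture may alter bleeding and hence sampling. The Background cites hormone changes in trials without a sham control, but the article has no data on bleeding. The mechanism is possible; its direction and size are conjecture.
- **That nothing can be done at analysis.** Adjustment for stage and recording of sampling type give partial repair. Only samples never taken are lost.

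**Conclusion.** The concern holds as a defect in the hormone sampling rule. Late-transition women with 2 to 11 months of amenorrhoea are placed in neither category at baseline, and most who stay amenorrhoeic are in neither at week 8. The week-8 statement rests on an assumed 12-month definition of menopause and uniform entry durations; moving the threshold to 11 months does not change the conclusion.

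The effect is confined to FSH, LH, FSH/LH and E2. Depending on how sites read the rule, these outcomes will have missing values in late-stage women or a mixture of timed and untimed samples. The number of women cannot be derived from the article, and no difference in bias between the arms is shown. The MRS primary outcome and its power are unaffected. The amendment is worth making, but the trial's main conclusion does not depend on it.

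**What to change.** Reconcile Methods/design, Inclusion criteria and Outcome as follows.

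1. At both baseline and week 8, replace the menopause category with women currently without menstruation, using the article's own late-transition definition (amenorrhoea over 60 days). State in both places when these women are sampled.
2. Record the sampling type, days 2 to 4 or untimed, on the case report form at each visit.
3. Compare hormones between groups by ANCOVA adjusted for the baseline hormone value and baseline transition stage, in place of the unadjusted test in item 6. Both covariates are fixed before treatment, and the primary outcome already has ANCOVA as an option.
4. Label any analysis restricted to women sampled the same way at both visits as exploratory, because it selects on bleeding after randomisation.

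The fix has a limit. Sampling type at week 8 will still depend on bleeding status at that visit, so the mixture is made visible and consistent across sites rather than abolished.

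The cost is one protocol sentence, one case report form field and a slightly longer analysis. The Trial status section reports 80 of 360 women recruited, so 360 − 80 = 280 had still to be enrolled when the article was written. For women already sampled, the type can be classified afterwards only if sample and menstrual dates were kept.
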